##### Monitoring, adverse events and study oversight

Information on trial monitoring, adverse events and study oversight is presented in online supplemental appendix 4.

10.1136/bmjopen-2021-060280.supp4Supplementary data

### Analysis

Quantitative outcomes will be analysed using simple descriptive statistics (eg, proportions and percentages, mean and SDs) and where appropriate, point estimates of effect sizes (eg, mean differences and relative risks) and associated 95% CIs. Analyses comparing the intervention and control groups will use the intention-to-treat principle, that is, all participants will be analysed in the treatment group to which they were randomised irrespective of compliance or other protocol deviation. Analysis will be conducted using Stata V.16.

For qualitative data, interviews will be audiorecorded and transcribed verbatim. NVivo V.12 will be used to manage, sort, code and organise the anonymised transcribed data. Interview transcripts will be analysed by GT using directed thematic analysis, using Braun and Clarke’s six-stage process,^28^ informed by the research aims.^29^

The health economics analysis will assess completion rates, estimate resources required to deliver the intervention and report simple descriptive statistics for resource use and outcomes. Key resource use items not currently specified on the form but included by participants will also be identified. The information will inform the cost and outcome data collection and identification of unit costs for a larger trial.

As this project is a training fellowship, the fellow (GT) will conduct the analysis and will have access to the whole dataset in order to conduct the trial. Therefore, it is not possible to conducted blinded analyses.

Data will be made available on reasonable request.

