### Sample size

The study will aim to recruit 60 participants (30 in the intervention group, 30 in the control group). As this is a feasibility study, no formal sample size calculation has been performed; however, the sample size is the estimated number that would be feasible to show that we can recruit these types of patients for this type of study.^26^

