### Randomisation

Participants will be randomised 1:1 to either the intervention or control group. A minimisation algorithm will be used within an online randomisation system to ensure balance in the treatment allocation using the following variables: age at consent (<60 years, ≥60 years); sex (male, female); diagnosis (TIA, minor stroke); employment (employed, non-employed/retired).

A ‘random element’ will be included in the minimisation algorithm, so that each patient has a probability, of being randomised to the opposite treatment that they would have otherwise received.

Participants will be randomised at baseline by clinical staff; however, to prevent baseline patient reported outcomes being affected by study arm allocation, participants will be notified of their randomisation allocation after they have returned the 1-week questionnaire or at 3 weeks (if the 1-week questionnaire is not returned). Participants will be notified of their allocation by a letter in the post, which will be sent by the research team at the Trials Unit. Due to the nature of the intervention, it is not possible to blind participants or clinicians delivering the intervention.

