Objective	Feasibility outcomes	Measurement of outcome
(A) Assess feasibility and acceptability of the trial design and methods	No of eligible/ineligible patients and reasons for ineligibility	Recruitment log
	Proportion of participants who consent face to face, verbal or postal	Registration log: method of consent
	Willingness of clinical staff to randomise patients	Interviews (clinical staff involved in randomisation)
	Recruitment and attrition rates	Registration log
	Response rates and frequencies of missing data: participant completed questionnaires and case report forms	1, 12 and 24 weeks questionnaires Case report forms
	End of study clinic appointment attendance rates	End of Study Clinic Appointment Form
	Acceptability of the trial design	Interviews (participants and clinical staff) Structured observations
(B) Provide data to inform the sample size for a definitive randomised controlled trial	SD of continuous patient reported outcome measures at 6 months	Patient reported outcome measure scores
	Recruitment and attrition rates	Registration log
(C) Provide data to help inform selection of the primary outcome measure for a definitive randomised controlled trial	Correlation of patient reported outcome measures	Patient reported outcome measure scores
	Patient reported outcome measure response rates and missing data	1, 12 and 24 weeks questionnaires

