##### Participant completed questionnaires

Participant completed questionnaires (1, 12 and 24 weeks) will be analysed for response rates and missing data. SDs of continuous PROMs at 6 months and correlation of PROMs will inform the sample size and selection of outcome measures for the definitive RCT. The intervention feedback questionnaire will report acceptability of the intervention. A paper copy of the feedback questionnaire and prepaid envelope will be posted to participants after the intervention appointment. This questionnaire contains 5-point Likert scale questions (eg, strongly agree—strongly disagree) and free text questions about experiences of the checklist, appointment and action plan.

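### The sizing outputs for the definitive trial stop at the raw 6-month SD: each outcome's own 1-week to 24-week correlation is not listed, and no adjustment for the 1-week score is mentioned

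*Protocol article*

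**What the plan says.** Supplying data for the sample size of a definitive RCT is one of the objectives in the Protocol article (Study objectives). Table 2, row B, names the outputs that serve it: "SD of continuous patient reported outcome measures at 6 months" and "Recruitment and attrition rates". The section on participant completed questionnaires says that "SDs of continuous PROMs at 6 months and correlation of PROMs will inform the sample size and selection of outcome measures". Study objectives and Table 2, row C, show which correlation is meant: that between different outcome measures, to help choose the primary outcome.

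Table 1 has the same PROMs completed at 1, 12 and 24 weeks. Under Randomisation, participants learn their allocation only after returning the 1-week form, or at 3 weeks if it has not come back. The stated reason is "to prevent baseline patient reported outcomes being affected by study arm allocation", so the protocol itself treats the 1-week score as the baseline.

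For between-arm comparisons, the Analysis section offers, where appropriate, "point estimates of effect sizes (eg, mean differences and relative risks) and associated 95% CIs" by intention to treat. It names no covariates.

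**The concern.** A trial with a continuous outcome measured before and after treatment is usually analysed with the early score as a covariate. Its sample size then depends on the residual variance, which needs two quantities: the SD at follow-up and the correlation of the measure with its own earlier value. This study withholds allocation to keep the 1-week score clean, but no listed sizing output uses that score. Correlations between different PROMs cannot stand in for it.

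What is at stake is the study's answer to its own sizing objective. A definitive trial planned from the raw SD alone could recruit more patients than it needs. A smaller loss is that the PROM differences reported here may have wider intervals than the data allow.

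**Working it through.** **Inputs from the Protocol article.** 30 per arm (Sample size); 80% return of 24-week questionnaires, the proceed threshold in Table 4; 95% intervals (Analysis). This gives 0.8 × 30 = 24 per arm, 48 in all. The 6-month SD is read as that of the 24-week questionnaire.

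**Assumed, because the document gives none.** Correlation r between the 1-week and 24-week scores of 0.3, 0.5 and 0.7. For the worked example, an effect of 0.3 SD, 80% power and two-sided 5% significance.

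There is no planned figure to reproduce: "As this is a feasibility study, no formal sample size calculation has been performed", and no size for the definitive trial is stated.

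**1. Effect on the definitive trial's size.** Required n is proportional to SD² for a raw comparison and to SD²(1 − r²) for ANCOVA. The excess from using the raw SD is 1/(1 − r²) − 1 = r²/(1 − r²).

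- r = 0.3: 0.09/0.91 = 10%
- r = 0.5: 0.25/0.75 = 33%
- r = 0.7: 0.49/0.51 = 96%

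Example: n per arm = 2 × (1.960 + 0.842)²/0.3² = 174.4, so 175. Multiplying 174.4 by 0.91, 0.75 and 0.51 gives 159, 131 and 89 after rounding up.

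**2. Precision of the SD.** With 48 analysed in two arms, df = 46. The 95% limits for the true SD, relative to the estimate, are √(46/66.6) = 0.83 and √(46/29.2) = 1.26.

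**3. Precision of the correlation.** For an observed r of 0.5 from 48 pairs, Fisher's z is 0.549 and its 95% margin is 1.96/√45 = 0.292. Transforming back gives about 0.25 to 0.69.

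**4. Interval width in this study, in SD units.** The unadjusted half-width is t(0.975, 46) × √(2/24) = 0.58. With k covariates it is multiplied by √(1 − r²) and by an approximate chance-imbalance factor √(1 + k/(45 − k)), and t is taken on 46 − k df. For five covariates, r stands for the total multiple correlation.

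| r | 1-week score only (k = 1) | 1-week score and four minimisation factors (k = 5) |
|---|---|---|
| 0 | 0.59 | 0.62 |
| 0.3 | 0.56 | 0.59 |
| 0.5 | 0.51 | 0.54 |
| 0.7 | 0.42 | 0.44 |

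Adjusting for the 1-week score alone gains precision at each r from 0.3 up. At r = 0 it costs about 1%. With all five covariates there is no gain at r = 0.3 (0.59 against 0.58).

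**The case against.** A reader might infer that the plan fixes unadjusted differences and that its intervals are therefore too wide. The text does not support that. The estimates are given as examples, the word unadjusted does not appear, and a regression model also yields a mean difference with a CI. Model and covariates are commonly left to an analysis plan, which is not shown. Whether the intervals are wider than necessary depends on an unstated correlation. This part therefore stands only as a point to state clearly.

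A reader might also infer that the definitive trial will be wrongly sized. That does not follow. Its size, target effect, primary outcome and analysis are all undecided; the SD is said only to inform the sizing; and the raw SD is the right input if that trial is analysed without adjustment. The missing correlation can also be computed later from data already collected.

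A third tempting step is to warn of lost power. If the SD estimate were 0.83 of the truth, 90% planned power for an unadjusted trial would fall to Φ(3.242 × 0.83 − 1.96) = 77%, but an estimate that low or lower arises only about 5% of the time. The two errors also pull in opposite directions: at r = 0.5 the raw SD exceeds the residual SD by 1/√0.75 = 1.155, and with 46 df the raw estimate would fall below the true residual SD only about 11% of the time.

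Finally, some 1-week forms will not come back. Dropping those participants would conflict with the intention-to-treat commitment, so an adjusted analysis has to deal with them.

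The core survives: row B of Table 2 is an explicit list of outputs for a stated objective, and it omits a quantity that the design already makes available.

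**Conclusion.** The point holds as an incomplete list of sizing outputs, with a lesser clarification for the between-arm estimates. If the definitive trial uses ANCOVA, the raw SD alone could oversize it by about 10% to 96% over assumed correlations of 0.3 to 0.7. In this study, adjusting for the 1-week score would narrow the 95% half-width at 24 per arm from 0.58 SD to about 0.51 at r = 0.5 and 0.42 at r = 0.7. Both results rest on correlations that the document does not give, and on 80% return.

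The consequence falls on planning the next trial. None of the quantitative progression criteria in Table 4 uses an effect estimate or its interval, so the decision to proceed is unaffected.

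**What to change.** In Table 2, row B, and in the matching sentence on participant completed questionnaires, add:

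- the pooled within-arm 24-week SD of each continuous PROM, with its 95% CI;
- for each candidate primary outcome, the 1-week to 24-week correlation of that same measure (or the residual SD after adjustment), with its 95% CI.

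In the Analysis section, state that continuous PROM differences are estimated by regression on arm and 1-week score. Use only 1-week forms completed before the allocation letter. Treat later forms as missing, and fill missing 1-week scores by a simple baseline imputation that ignores arm, so that intention to treat is kept. Adding the four minimisation factors is optional, since at about 48 analysed they can cancel the gain when r is low. Using an upper confidence limit of the SD as the planning value is a debatable trade-off and is better left to the team that designs the definitive trial.

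The cost is wording only, with no new data. The downsides are one or a few degrees of freedom, a rule for missing 1-week forms, and a correlation that is itself imprecise (about 0.25 to 0.69 for an observed 0.5 from 48 pairs), which is why it should be reported with its interval.

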### Progression criteria

The predefined progression criteria, detailed in table 4, will be used to inform a decision on whether a full RCT is warranted and feasible. The criteria were agreed by the Study Oversight Committee and follow a traffic light system using quantitative measures supported by qualitative data.

**Table 4 T4:** Progression criteria

Key uncertainties	Measures used	Progression criteria
**Trial design**		
Recruitment	% target sample size recruited	≥90%: proceed to a full-scale trial
		70%–89%: SOC will consider the feasibility of proceeding to a full-scale trial bearing in mind the data presented, representativeness of the sample and possible steps to increase recruitment.
		<70%: full-scale trial unlikely to be feasible
Randomisation*	% of consented participants randomised	≥90%: proceed to a full-scale trial
		70%–89%: SOC will consider the feasibility of proceeding to a full-scale trial bearing in mind the data presented, representativeness of the sample and possible steps to address randomisation issues.
		<70%: full-scale trial unlikely to be feasible
Return rate of 24 weeks questionnaire*	% of 24 weeks questionnaires returned	≥80%: proceed to a full-scale trial
		50%–79%: SOC will consider the feasibility of proceeding to a full-scale trial bearing in mind the data presented, representativeness of the sample and possible steps to increase return rates.
		<50%: full-scale trial unlikely to be feasible
Intervention		
Attendance rate*	% of intervention arm participants attending first appointment	≥90%: proceed to a full-scale trial
		70%–89%: SOC will consider the feasibility of proceeding to a full-scale trial bearing in mind the data presented, representativeness of the sample and possible steps to increase attendance
		<70%: full-scale trial unlikely to be feasible
Delivery of the intervention	% completion of: checklists, action plans, GP letters; use of directory of support services; Issues regarding delivery of the intervention components and contamination explored in qualitative interviews	The SOC will consider the quantitative and qualitative data and make an overall judgement on whether the intervention content is delivered as intended
Acceptability	% of participants reporting acceptability of intervention components on intervention feedback questionnaire; issues regarding acceptability of the intervention components explored in qualitative interviews	The SOC will consider the quantitative and qualitative data and make an overall judgement on whether the intervention is acceptable

*Critical progression criteria: the trial is unlikely to be feasible if these criteria are not met, even if other criteria are satisfactory.

GP, general practitioner; SOC, Study Oversite Committee.

## Ethics and dissemination

Favourable ethical opinion was gained from the Wales Research Ethics Committee (REC) 1 (23 February 2021, REC reference: 21/WA/0036). Study results will be published in a peer-reviewed journal and presented at relevant conferences. A lay summary and dissemination strategy will be codesigned with consumers. The lay summary and peer review publication will be distributed on social media.
